## Methods: participants, interventions, and outcomes

### Study setting {9}

Participants will be recruited in German-speaking countries, mainly Germany and Austria. Recruitment will cover both urban and rural areas. The study is not limited to specific occupations or sectors but includes all shift-working occupational groups. Due to the nationwide recruitment of subjects, treatments will be administered in an online setting.

### Eligibility criteria {10}

Included are people of all genders, aged 18 to 65, who work shifts for at least 30 h a week and suffer from primary insomnia. We excluded people with pre-existing physical conditions such as sleep apnoea, restless legs syndrome or chronic pain. We also excluded people with a history of mental disorders, namely severe affective or anxiety disorders, acute substance abuse disorders, and psychotic or schizo-affective disorders.

The assessment of the inclusion criteria by means of interviews and the implementation of the interventions will be carried out by psychology master students from the University of Salzburg, who already have clinical experience and have undergone specific training.

### Interventions {11a}

Treatments in both conditions are delivered online by MS Teams in groups of 12 people with one trainer per group. Both conditions receive seven sessions over 7 weeks of 90 min each. As a starting point, the CBT-I-S group receives reading information material 1 week before the first session. The standard CBT-I condition starts keeping a sleep diary 1 week before the first session.

The implementation will start when enough participants have been found for two parallel groups per condition, to be able to take an alternative appointment in the parallel group in case of scheduling problems.

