### Sample size {14}

To determine the required sample size, a power estimation was carried out with G*Power [38]: ANOVA with repeated measures and within-between interactions, 2 groups and 3 measurement times, small expected effect 0.1, desired power of 0.80 (1-β), *p* = 0.01 (4 outcome variables), correlation among repeated measures 0.7 results in a total sample size of *N* = 142.

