### Statistical methods {20 a-c}

For analysing primary and secondary outcomes, we will use linear mixed-models:

We will make within-subject comparisons of the primary and secondary outcomes at the three time points before and after treatment and at follow-up. We will also make between-subject comparisons, i.e., a comparison of the three conditions at the three time points.

Mediator and moderator analyses of the moderation and mediation of the outcomes: No hypotheses about mediators and moderators will be formulated. These analyses are purely exploratory.

We expect low attrition at the post-measurement, but somewhat higher at the follow-up measurement. Individuals who did not complete the post-measurement will be excluded. Those who did not complete only the follow-up may be included in the pre-post comparison but must be excluded from the calculations of the stability of the effects. Depending on their number, it may be necessary to analyse whether they represent a group with specific characteristics. As no post- or follow-up data is expected to be available from the dropouts, an intention-to-treat analysis is not possible. Instead, a per-protocol analysis will be conducted with all participants who were present in at least 4 sessions.

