### Auditing {23}

During the delivery of treatment, the trainers are supervised separately according to the conditions. Supervision is provided by two experienced therapists who are independent of the trial management and sponsor.

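### N = 142 assumes independent participants, but both arms are treated in groups of 12, so 1% error and 80% power cannot both hold if outcomes correlate within therapy groups

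*Protocol article*

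**What the plan says.** Interventions {11a} describes delivery in both arms: "Treatments in both conditions are delivered online by MS Teams in groups of 12 people with one trainer per group". Recruitment must fill two parallel groups per condition before treatment starts, so that a participant with a scheduling problem can attend the other group. Background and rationale {6} adds that a missed session can be made up by reading or watching the content online.

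Sample size {14} bases N = 142 on "ANOVA with repeated measures and within-between interactions, 2 groups and 3 measurement times", with "small expected effect 0.1", power 0.80, p = 0.01 to allow for four outcomes, and "correlation among repeated measures 0.7". It mentions no ICC, design effect or number of therapy groups.

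Statistical methods {20 a-c} names linear mixed models and then lists the comparisons. The first is "We will make within-subject comparisons of the primary and secondary outcomes at the three time points before and after treatment and at follow-up"; a between-subject comparison of the conditions follows. The random effects are not stated.

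On trainers, Auditing {23} says: "During the delivery of treatment, the trainers are supervised separately according to the conditions".

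**The concern.** Participants are randomised individually but treated together. From the first session on, members of one therapy group share a trainer, a set of fellow participants and a course of discussion. Randomisation balances the arms at baseline; it does not remove correlation that arises afterwards. With about six groups per arm, differences between groups do not average out as they would over 71 independent people.

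The purpose of the trial is to show superiority of CBT-I-S over CBT-I, and the Strengths section presents N = 142 as a gain in statistical power. If the groups matter, either the trial has less power than stated, or, if the groups are left out of the model, an unusually good group or trainer can pass for a better manual more often than 1 time in 100.

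**Working it through.** **Inputs from the protocol article.** Two arms, three measurement times (m = 3), f = 0.1, correlation 0.7, alpha 0.01, power 0.80, N = 142 (Sample size {14}); equal allocation (Trial design {8}); groups of 12 with one trainer each (Interventions {11a}).

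**Assumed input.** The ICC, from 0.01 to 0.10. It is taken on the scale of the within-participant time contrasts that the interaction test uses, so that power and type I error refer to the same scenario.

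**Step 1: reproduce N = 142.** For the within-between interaction:

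- Noncentrality: λ = f² × N × m / (1 − ρ) = 0.01 × 142 × 3 / 0.3 = 14.2
- Degrees of freedom: (2 − 1)(3 − 1) = 2 and (142 − 2) × 2 = 280
- Power at alpha 0.01 from the noncentral F distribution: 0.803. At N = 140 it is 0.796.

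So 142 is the smallest even total that reaches 0.80, under independence and with nothing added for therapy groups.

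**Step 2: number of groups.** 142 / 12 = 11.8, so about 12 groups, 6 per arm.

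**Step 3: power at a valid 1% level.** The design effect is DE = 1 + (12 − 1) × ICC. The effective sample size is 142 / DE, and λ shrinks to 14.2 / DE.

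| ICC (assumed) | DE | Effective N | λ | Power |
|---|---|---|---|---|
| 0.01 | 1.11 | 128 | 12.8 | 0.75 |
| 0.02 | 1.22 | 116 | 11.6 | 0.69 |
| 0.05 | 1.55 | 92 | 9.2 | 0.55 |
| 0.10 | 2.10 | 68 | 6.8 | 0.38 |

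These values still use a large error degrees of freedom. Twelve groups leave only 12 − 2 = 10 between-group degrees of freedom per contrast. In a simulation of 2 × 6 groups of 12 (N = 144) with the therapy group as error term, power was 0.64 / 0.57 / 0.45 / 0.30.

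**Step 4: type I error if the therapy group is left out.** The same simulation without a treatment effect (20,000 runs per cell), tested at participant level at nominal 1%:

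| ICC (assumed) | Therapy group ignored | Therapy group as error term |
|---|---|---|
| 0.01 | 1.6% | 1.1% |
| 0.02 | 2.2% | 1.0% |
| 0.05 | 5.4% | 1.0% |
| 0.10 | 11.5% | 1.1% |

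With f = 0.1, the participant-level test still rejects in 77% to 81% of runs. Ignoring the groups therefore keeps the apparent power and gives up the error level; modelling them does the reverse.

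**Scale of the ICC.** An ICC expressed on the total variance of post-treatment scores is larger on the change scale. With correlation 0.7, the change from baseline to the mean of the two later measurements has variance 1 + (1 + 0.7)/2 − 2 × 0.7 = 0.45 in units of the score variance. A group component of 0.02 shared by both later measurements is then 0.02 / 0.45 ≈ 0.04 of it. Any ICC used in a restated calculation needs its scale named.

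**The case against.** The strongest reply is that a linear mixed model can carry a therapy-group effect, and that the random-effects structure is commonly left to an analysis plan, which is not shown here. This stands. A reader might infer from Statistical methods {20 a-c} that the analysis treats participants as independent and that its standard errors are too small. The article does not say so: it names subject-level comparisons and leaves the random effects open. The type I error figures are therefore conditional on the group being left out. A group effect in an unseen plan would restore the 1% level. It would not restore the 80%, because N holds no allowance.

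Nor do inflated error and lost power occur together. They are alternatives that depend on the model.

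Two further readings go too far:

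- **Trainer and group as the same unit, with trainers nested in one arm.** Interventions {11a} gives one trainer per group, not one group per trainer. Auditing {23} describes supervision, not how trainers are assigned.
- **The protocol itself expects clustering.** Limitations says that mixing occupations might influence group dynamics and effectiveness, and separately that cohesion may suffer online. Neither statement says that outcomes correlate within therapy groups.

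The ICC may also be small. Attending the parallel group or making up sessions by self-study blurs membership and may lower it, and at 0.01 the loss is modest. The article gives no basis for assuming a value that low.

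**Conclusion.** The concern holds for the sample size and conditionally for the analysis. N = 142 gives 80% power at the 1% level only for independent participants, and treatment in groups of 12 makes that assumption doubtful. For any positive ICC the two stated figures fail as a pair. With the groups modelled, power is about 0.75 at ICC 0.01 and 0.38 at ICC 0.10 before the loss from few degrees of freedom. With the groups omitted, type I error is about 1.6% to 11.5% over the same range.

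The direction is firm. The size rests on an assumed ICC, fixed groups of 12 and about 12 groups. Because the ICC is unknown and the random effects are unstated, this is a point that should be fixed rather than one that invalidates the plan.

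**What to change.** - **Sample size {14}:** replace the unqualified 0.80 with power over a stated ICC range, naming the scale of the ICC and allowing for the small number of groups. N need not be enlarged; recruitment is already reported as difficult.
- **Statistical methods {20 a-c}:** include a random effect for the therapy group first assigned, acting on the post-baseline measurements. Add a trainer effect if any trainer leads more than one group. Test the treatment contrast with Satterthwaite or Kenward-Roger degrees of freedom. If an analysis plan already does this, a sentence confirming it is enough.
- **Data:** record therapy-group and trainer identifiers for every participant.

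The cost is one or two variance components in a model already planned and two data fields. Confidence intervals become wider and the stated power less favourable.

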#### CBT-I-S (experimental condition)

This group will receive psychoeducation 1 week in advance as self-study reading material. The sessions will have the following contents:Introduction, discussion of reading material, derivation of the therapeutic rationale, attitude to shift workTips for shift work, positive activities, relaxation, daily structureProblem solving, acceptance, resource orientation(Depressive) ruminationFear/anxiety/worryMoodConclusion: exchange of experiences, emergency kit, farewell[4–6, 17, 25–35]

#### CBT-I (standard condition)

From 1 week before the first session until the last session, this group keeps a sleep diary. Session 1 to 7 will have the following contents:Introduction, psychoeducation, relaxationIntroduction of sleep restriction, calculation of sleep windowDeepen sleep restriction, repeat relaxationStimulus controlSleep hygienecognitive restructuringExchange of experiences, sleep protocols, relapse prevention, farewell[14, 29–31, 36, 37]

Sleep restriction is not easy to implement for shift workers, but should nevertheless be applied in the standard group, in a slightly adapted form: The reduction of total time in bed to total sleep time is emphasised as the main effective factor. In order not to jeopardise the compliance of shift workers, less emphasis is placed on the regularity of the sleep window.

### {11b}

The interventions will be stopped or modified if, contrary to expectations, the trainers notice a deterioration in individual participants during the sessions, or if participants contact the study management with complaints.

### {11c}

Participants are motivated to take an active part in the sessions. Attendance is monitored through homework, which is discussed during the sessions, and through the trainers’ assessment of participation in the group.

### {11d}

During the course of therapy, subjects should not receive any other treatment for sleep disorders. If someone is in therapy for other reasons, they may not need to be excluded. This must be assessed on an individual basis. Occasional use of sleeping pills is allowed.

### Outcomes {12}

The primary outcome is improvement in the following key sleep variables: total sleep time, sleep onset latency, subjective sleep quality and daytime sleepiness. We also want to measure the severity of the sleep disorder.

Secondary outcomes are improvements in depressive mood and anxiety, dysfunctional sleep attitudes, and cognitive and physiological arousal.

Data will be collected at three time points: before starting treatment, at its end and 6 months later as a follow-up. We will compare group means between groups and within groups at each time point. Since we will have multiple primary outcomes over multiple time points, we will adjust the α-level using a Bonferroni correction.

The magnitude of the differences, especially in the pre-post comparisons, should not only be statistically, but also clinically significant. This means, for example, that subjects no longer meet the criteria for a sleep disorder (DSM-5, [11]) after treatment.

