### Objectives {7}

To test these hypotheses, a newly developed insomnia treatment for shift workers (CBT-I-S) will be compared with the classical treatment of sleep disorders (CBT-I). The working hypothesis is that the experimental condition (CBT-I-S) will produce significant improvements in total sleep time, sleep onset latency, subjective sleep quality and daytime sleepiness in shift workers. These positive effects will be clearly superior to those of the standard condition (CBT-I) and will remain stable for 6 months after the end of treatment.

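### Single-step Bonferroni for the primary outcomes is valid, but Holm's step-down procedure gives the same family-wise error and more power if several effects are real

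*Protocol article*

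**What the plan says.** Outcomes {12} gives the reason for adjusting, "Since we will have multiple primary outcomes over multiple time points", and the method: "we will adjust the α-level using a Bonferroni correction". It states neither the overall alpha nor the number of tests, and the article names no step-down procedure.

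The primary outcomes in that section are "total sleep time, sleep onset latency, subjective sleep quality and daytime sleepiness. We also want to measure the severity of the sleep disorder". The Insomnia Severity Index (ISI), which measures that severity, is listed under the primary outcomes in Data collection methods {18a}. The family could therefore hold four outcomes or five.

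Sample size {14} uses "ANOVA with repeated measures and within-between interactions, 2 groups and 3 measurement times", "small expected effect 0.1", "desired power of 0.80 (1-β" and a significance level of "0.01 (4 outcome variables", with a correlation of 0.7 over time. The result is N = 142.

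Objectives {7} hypothesises "significant improvements in total sleep time, sleep onset latency, subjective sleep quality and daytime sleepiness" under the new therapy, and expects these effects to exceed those of standard CBT-I.

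**The concern.** Single-step Bonferroni holds every outcome to alpha/m, whatever the other outcomes show. Holm orders the p-values and tests the smallest at alpha/m, the next at alpha/(m-1), and so on up to alpha, stopping at the first failure. With four tests at 5% the steps are 0.0125, 0.0167, 0.025 and 0.05. Holm needs no assumption about the dependence between outcomes, and neither does Bonferroni. It controls the same family-wise error and rejects everything that Bonferroni rejects.

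The step-down helps most when several effects are real, and the Objectives hypothesise benefit on all four outcomes. Recruitment is this trial's stated difficulty: an arm was cancelled and a payment was added. Power that needs no extra participants is therefore worth having.

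**Working it through.** **Inputs from Sample size {14}:** N = 142, k = 2 groups, m = 3 times, f = 0.1, correlation over time 0.7. **Assumed, because the article does not give them:** overall two-sided alpha 0.05; correlation between outcomes from 0 to 0.7; sphericity; equal effects; no dropout; no clustering by therapy group.

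**1. The article's own figure.** For the within-between interaction:
- lambda = f² × N × m / (1 − rho) = 0.01 × 142 × 3 / 0.3 = 14.2
- df1 = (2 − 1)(3 − 1) = 2; df2 = (142 − 2)(3 − 1) = 280

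At alpha 0.01 the noncentral F gives 80.3% power, and 142 is the required N. The stated figure reproduces.

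**2. The level.** For four tests, 0.05/4 = 0.0125. At that level 136 participants suffice, and 142 give 82.4%. The 0.01 used for sizing equals 0.05/5, and over four tests its Bonferroni bound is 4 × 0.01 = 0.04. The comparison below uses 0.0125 for Bonferroni, so that both methods spend the same overall 5%.

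**3. Bonferroni against Holm.** Four tests, N = 142, F on 2 and 280 df with lambda 14.2 for each real effect, 100,000 simulated trials per setting. Ranges run over the assumed correlation between outcomes.

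| Real effects | Quantity | Bonferroni (0.0125) | Holm |
|---|---|---|---|
| four | power per outcome | 82.4% | 88.5-91.2% |
| four | power for all four | 46-65% | 73-81% |
| four | power for at least one | 95.2-99.9% | the same |
| two | power per real outcome | 82.4% | 84.1-84.7% |
| one | power for that outcome | about 82.5% | about 82.5% |
| none | family-wise error | 3.8-5.0% | the same |

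A check by hand: with independent outcomes, Bonferroni power for all four is 0.824⁴ = 0.46, the lower end of the range. The Holm gain for all four is 27 points at correlation 0 and 17 points at 0.7. The at-least-one row is equal because Holm's first step is the Bonferroni level.

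**4. If the ISI is a fifth primary outcome.** Both methods then start at 0.05/5 = 0.01. With all five effects real, power per outcome goes from about 80% to 87.5-90.6%, and power for all five from 33-59% to 68-79%. With two real, it goes from about 80% to about 82% per outcome.

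**5. If the family were four outcomes by three time points.** The level is 0.05/12 = 0.00417. Bonferroni power at N = 142 is 71.4%, and N = 164 would be needed for 80%. Holm gives 82-86% only if all 12 effects are real, and about 72% if two are. All 12 cannot be expected for between-arm tests, because the four baseline comparisons are null in expectation under randomisation. Holm does not rescue a family that is drawn too wide.

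**The case against.** Bonferroni is valid and pre-specified, and the planned 80% per outcome is already met at the level used for sizing. A reader might infer from this point that the plan is in error or underpowered because of Bonferroni. The article does not support that: N = 142 reproduces, and the choice of Bonferroni contradicts nothing. This part of the objection stands in full.

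A reader might also infer that Holm gives clearly more power in every case. It does not. The large gain needs most or all effects to be real, and with one or two it is negligible or small. Setting the power at 0.01 beside Holm would also overstate the gain, because it mixes the move from 0.01 to 0.0125 with the move to a step-down. Outcomes {12} fixes no numerical level, so the fair comparison is at equal overall alpha.

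Third, if success required benefit on all four outcomes jointly, no splitting of alpha would be needed and Holm would not be the natural remedy. The article states no such joint rule, and its choice of an adjustment points to separate claims. The per-outcome gain is then the main measure, and the all-four figure describes how often the whole hypothesis would be shown.

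Fourth, Holm needs a defined family just as Bonferroni does, and the article leaves it unclear: outcomes and time points in one section, four outcomes at 0.01 in another, the ISI among the primary measures in a third. This stands, and the fix has to settle it.

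Last, Bonferroni has simple simultaneous intervals that match its tests. That is a real but small cost of changing. The interaction test used for sizing has 2 df, so no single interval mirrors it under either method.

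**Conclusion.** The point holds as a suggestion on efficiency. For the same family and overall alpha, Holm never does worse than the stated Bonferroni correction. Under the article's own hypothesis of benefit on all four outcomes, it adds 6 to 9 points of power per outcome and 17 to 27 points for showing all four. The gain falls to about 2 points per outcome with two real effects, and to practically nothing with one.

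The direction does not depend on the assumptions, because Holm's dominance is a mathematical fact. The sizes do depend on them. Attrition, treatment in groups of 12 and the planned per-protocol analysis would change the absolute powers.

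**What to change.** In Outcomes {12}, replace the reference to a Bonferroni correction by: *Holm step-down procedure at two-sided family-wise 5% over the confirmatory between-arm (group-by-time) tests, one per primary outcome.* State in the same sentence how many outcomes the family holds: four, or five if the ISI is primary. Within-group and single-time-point comparisons then fall outside the confirmatory family.

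Keep N = 142. It was sized at 0.01, which is stricter than Holm's first step with four outcomes (0.0125) and equal to it with five. It is conservative only as to the significance level, since it holds no allowance for dropout or clustering.

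The cost is one sentence, fixed before outcome data are analysed. Because Holm-consistent simultaneous intervals are less simple, report unadjusted intervals, labelled as such, beside Holm-adjusted p-values. Say that the two can disagree: an unadjusted 95% interval may exclude zero while the adjusted p-value exceeds 0.05.

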### Participant timeline {13}

See the participant timeline in Fig. 1. The period between *t*_1_ and *t*_2_ is 8 weeks, and the period between *t*_2_ and *t*_3_ is 6 months.

**Fig. 1 Fig1:**
[figure not shown]
Participant timeline

### Sample size {14}

To determine the required sample size, a power estimation was carried out with G*Power [38]: ANOVA with repeated measures and within-between interactions, 2 groups and 3 measurement times, small expected effect 0.1, desired power of 0.80 (1-β), *p* = 0.01 (4 outcome variables), correlation among repeated measures 0.7 results in a total sample size of *N* = 142.

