#### Primary outcomes

PSQI: Pittsburgh Sleep Quality Index [40, 41]. This questionnaire measures sleep onset latency, total sleep time and subjective sleep quality. The re-test reliability is good, *r* = 0.82–0.89 [40], Cronbach’s *α* is also good with a value of 0.80 [41], the diagnostic validity is over 80% (sensitivity) or between 83 and 87% (specificity; quoted from [40]). So it can also be considered good.ESS: Epworth Sleepiness Scale [42], to measure daytime sleepiness. Cronbach’s α is acceptable to good with values between 0.73 and 0.88. According to Kendzerska et al. [43], re-test reliability is only described as good by one study with a value of *r* = 0.82, other studies found lower values. In their meta-analysis, Kendzerska et al. [43] found medium validity.ISI: Insomnia Severity Index [44], to assess severity of sleep disorder. According to [45], quality criteria are overall acceptable to good: Cronbach’s *α* = 0.74–0.78. In the opinion of these authors, further findings on concurrent validity and reliability are evidence that it is a valid and sensitive instrument.

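### The 0.01 level behind N = 142 matches neither the four outcomes cited for it nor the Bonferroni rule in the Outcomes section; 80% power is in doubt only if time points enter the divisor

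*Protocol article*

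**What the plan says.** Three places in the protocol article bear on the significance level.

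- **Sample size {14}** gives a G*Power calculation for a repeated-measures ANOVA, within-between interaction, with 2 groups, 3 measurement times, effect 0.1 and power 0.80. The level and correlation are given as "0.01 (4 outcome variables), correlation among repeated measures 0.7", and the result is N = 142. This is the only numerical significance level in the document.
- **Outcomes {12}** lists as primary "total sleep time, sleep onset latency, subjective sleep quality and daytime sleepiness. We also want to measure the severity of the sleep disorder". That is four named variables, with severity added in a separate sentence. The multiplicity rule is: "Since we will have multiple primary outcomes over multiple time points, we will adjust the α-level using a Bonferroni correction". No overall alpha, divisor or per-test level follows. The same section plans these comparisons: "We will compare group means between groups and within groups at each time point".
- **Primary outcomes**, under Data collection methods {18a}, includes "ISI: Insomnia Severity Index [44], to assess severity of sleep disorder". Under that heading there are five primary outcomes.

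**The concern.** The sample size section gives a level and a count, and the Outcomes section gives a rule. They do not fit together.

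1. On an overall 0.05, the level does not follow from the count of four.
2. The count differs between sections, four or five, depending on whether the ISI is primary.
3. The rule names time points as a second reason for correcting, and the level used for sizing makes no allowance for them.

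At stake is the threshold at which superiority of CBT-I-S is claimed. With several primary outcomes and no blinding, an unsettled threshold could be chosen once the p-values are known. The second question is whether the 80% power attached to N = 142 belongs to the test that will decide the trial.

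**Working it through.** **Inputs.** From Sample size {14}: k = 2 groups, m = 3 times, f = 0.1, ρ = 0.7, α = 0.01, target power 0.80. Equal allocation is from Trial design {8}. Two inputs are assumed because the protocol does not give them: overall alpha 0.05, and sphericity (ε = 1).

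**Step 1: reproduce N = 142.** For the within-between interaction, power comes from a noncentral F distribution with

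λ = f² · N · m / (1 − ρ) = 0.01 × 142 × 3 / 0.3 = 14.2,

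df1 = (k − 1)(m − 1) = 2, df2 = (N − k)(m − 1) = 140 × 2 = 280.

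At α = 0.01 power is 80.3% for N = 142 and 79.6% for N = 140. The stated N reproduces.

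**Step 2: which count gives 0.01?**

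- Four outcomes: 0.05/4 = 0.0125
- Five outcomes: 0.05/5 = 0.01

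So 0.01 is the exact Bonferroni level for five outcomes. Applied to four, it spends 4 × 0.01 = 0.04 in total, which is valid but slightly conservative.

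**Step 3: power if only outcomes are counted** (same test, N = 142, all analysed).

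| Primary outcomes | Per-test α | Power at N = 142 | N for 80% |
|---|---|---|---|
| 4 | 0.0125 | 82.4% | 136 |
| 5 | 0.01 | 80.3% | 142 |

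The 80% holds in both rows.

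**Step 4: levels if time points also enter the divisor.** The protocol gives no divisor, so this is a range of readings.

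- Two post-baseline times: 0.05/8 = 0.00625 (four outcomes) or 0.05/10 = 0.005 (five)
- All three times: 0.05/12 = 0.0042 (four) or 0.05/15 = 0.0033 (five)

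None of these is 0.01. Testing at 0.01 would spend 8 × 0.01 = 0.08 over eight tests and 12 × 0.01 = 0.12 over twelve.

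**Step 5: what power would then mean.** The test in Step 1 covers all three times in one test per outcome, so there are only four or five such tests. A divisor of 8 to 15 arises only for comparisons made separately at each time, and their power has to be worked out for that contrast.

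As an illustration, assume that f = 0.1 arises from an equal standardised group difference d at post and follow-up and none at baseline. The group differences are (0, d, d), with mean 2d/3. Half of each deviation from that mean gives the cell interaction effects, of size d/3, d/6 and d/6. Then

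f² = (d²/9 + d²/36 + d²/36)/3 = d²/18, so d = 0.1 × √18 = 0.424.

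For one post-baseline time, 71 per arm, two-sided α = 0.05/12, the noncentrality is (d/SD) × √(71/2):

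| Analysis at one time | Residual SD | Noncentrality | Power |
|---|---|---|---|
| Raw scores | 1 | 2.53 | 35% |
| Change from baseline | √(2 × 0.3) = 0.775 | 3.26 | 64% |
| Baseline-adjusted | √(1 − 0.7²) = 0.714 | 3.54 | 73% |

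Under this assumption power is below 80% in all three, and the size of the shortfall depends on the analysis chosen.

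**The case against.** The strongest reply is that the document states only one level, 0.01, and that this level controls error at 0.05 for either four or five outcomes. The clause about time points explains why a correction is made; it is not a formula. The exact divisor is also something that an analysis plan commonly fixes.

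Much of this stands. 0.01 is usable as it is for a family of four or five tests, N = 142 is correctly calculated, and a missing divisor alone would not be a finding. What remains is that the statements made here disagree: a level explained by a count that does not produce it, two sections that differ on whether the ISI is primary, and a rule that cites time points which the sizing does not allow for.

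A reader might go further and infer that the trial lacks its stated 80% power. The protocol does not support that. No passage sets a divisor that includes time points, and without one the power is kept.

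A reader might also put the smaller levels into the calculation of Step 1. That gives 75.7% at 0.05/8, 71.4% at 0.05/12 and 69.0% at 0.05/15. Those figures should not be quoted as the trial's power, because they apply a test that already spans all times at a level meant for time-specific comparisons. Divisors of 12 and 15 also count the baseline comparison, which is not a test of efficacy.

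**Conclusion.** The inconsistency is real and concerns the threshold on which the superiority claim depends. With an assumed overall alpha of 0.05, the level of 0.01 fits five primary outcomes and not the four given as its basis, and it does not reflect the time points named in the Bonferroni rule.

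The effect on power is conditional. With one group-by-time test per outcome, N = 142 keeps at least 80% power under either count. If time points are counted, the stated 80% has no basis. These results rest on overall alpha 0.05, sphericity, and all 142 participants being analysed. The last is optimistic, because Statistical methods {20 a-c} excludes anyone without a post-measurement and limits the analysis to those present in at least 4 sessions.

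**What to change.** Before any outcome data are analysed:

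1. State the overall alpha.
2. Make Outcomes {12}, Sample size {14} and the Primary outcomes list agree on whether the ISI is primary.
3. Define one confirmatory group-by-time test per primary outcome. With four outcomes, set α = 0.0125. With five, keep α = 0.01 and change the sample size text to say five outcome variables.
4. In Outcomes {12}, remove time points from the Bonferroni count, and describe time-specific and within-arm comparisons as follow-up tests.

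If time points are to stay in the divisor, state the divisor, name the between-group contrast tested at each time, and replace the 80% with the power of that contrast at that level. It should not be read off the omnibus interaction test.

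Steps 1 to 4 cost only wording in three sections, with no extra participants or data. Keeping time points in the divisor would need a new power calculation and might show that N = 142 is too small for 80%.
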